#### Questionnaires for subjective assessment of xerostomia

Patients will complete the Visual Analog Scale (VAS) questionnaire and the Xerostomia questionnaire, before the procedure, at the follow-up visits at 4 weeks and 4 months after the procedure.^29,30^ The VAS questionnaire consists of 8 questions that assess two basic aspects of salivary secretion: mucosal dryness and functional abilities (swallowing, speaking) resulting from mucosal dryness. Patients are asked to mark their response on a 100-mm horizontal line for each question.^29^ The Xerostomia questionnaire also consists of eight questions: the first four questions refer to dryness of the mucous membranes during eating or chewing, whereas the last four questions refer to situations in which the person does not eat or chew. Patients rate each symptom on an 11-point Likert scale from 0 to 10, with a higher number indicating more pronounced dryness or greater discomfort due to lack of saliva.^30^

#### Quality of life assessment questionnaire

Patients will complete the European Organization for Research and Treatment of Cancer (EORTC) Quality of Life Questionnaire Head and Neck Module (QLQ-H&N35) before procedure and at follow-up visits at 4 weeks and 4 months after procedure. This questionnaire consists of 35 questions divided into seven domains and 11 individual questions. The questionnaire assesses symptoms and side effects of head and neck cancer treatment, social integration, and sexual functioning. Questions are rated using a four-point Likert scale, except for the last five questions, which offer two response options (yes/no).^31^

#### Blood tests

Venous blood samples will be collected before the procedure and at the follow-up visits 4 weeks and 4 months after the procedure, following the blood collection protocol used at the Institute of Oncology Ljubljana. The values of standard parameters of complete blood count, differential blood count, liver function tests, as well as electrolyte levels, renal markers, total proteins, albumin and C-reactive protein will be analyzed. Prothrombin time and international normalized ratio will also be determined during the first blood draw.

## Intervention

MSC-based investigational medicinal products (IMPs) will be prepared at the Slovenian Institute for Transfusion Medicine according to validated standard operating procedures approved by the National Medical Ethics Committee (No. 0120-60/2018/7, 24.4.2018). The umbilical cord tissue will be used as the primary biological source. The tissue is first seeded in an *ex vivo* culture. After the first 10–14 days (passage 0), adherent cells begin to proliferate extensively and reach adequate confluence within the next 7 days. They are then harvested in passage 0 and reseeded for further cell expansion (passage 1). At the end of passage 1, cells from 4 different donors are harvested and pooled into a single cell suspension in equal ratios. They are then redistributed into identical aliquots and cryopreserved as “off-the-shelf units” (EQ-MSC) available for “per patient” orders. For each patient, an identical aliquot of EQ-MSCs is thawed and seeded in cell culture for 3–5 days prior to the procedure (passage 2) to achieve optimal numbers and cell fitness for the final product. The final drug formulation will be prepared as a suspension of 50×10^6^ MSCs/ml in a physiological solution with an addition of 0.5% human albumin. It will be filled in syringes of 0.5 ml or 1.0 ml with a 23G 0.6×25 mm hypodermic needle.

In the intervention group, each patient will receive an ultrasound-guided injection of 50×10^6^ MSCs into each parotid gland and an injection of 25×10^6^ MSCs into each submandibular gland, without anesthesia. To ensure even distribution of the MSC suspension, each parotid gland will receive injections in two areas: the tail and the body of the gland.

Approximately 5% of the volume of the prepared MSC injectate will be removed under aseptic conditions. The cells will be labeled with hexamethylpropyleneamine oxime ([99mTc]Tc-HMPAO) and resuspended with the remaining injection material for administration to the patient.

### Course of the study

After the procedure (day 0), patients (intervention group) will be examined at day 1, day 5, after 4 weeks, and after 4 months. An assessment of toxicity will be performed at each visit. At 4 weeks and 4 months after the intervention, the same measurements and questionnaires will be performed as when patients were enrolled in the study, except for core needle biopsy and scintigraphy, which will be repeated only at 4 months (Figure 1).

No follow-up is scheduled for the volunteers (control group) after enrollment in the study and the initial examinations (day 0).

The study will continue until completion of follow-up for the last enrolled patient or for a maximum of two years. Tentatively, the study is expected to run from October 2023 to September 2025.

### Termination guidelines

The study will be terminated early if serious adverse events are noted during the intervention or follow-up. An allergic reaction, injection site infection, or other local or systemic event assessed as possibly/probably/surely related to the intervention and graded according to CTCAE v5.0 grade 3 or higher (serious adverse reaction, SAR) will be considered a discontinuation criterion. If a SAR is registered, the principal investigator will notify the study coordinator within 24 hours and later the National Center for Pharmacovigilance of the Agency for Medicinal Products and Medical Devices of the Republic of Slovenia and the Ethics Committee of the Institute of Oncology Ljubljana.

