## Methods and design

The study is being conducted at the Institute of Oncology Ljubljana in collaboration with the Slovenian Institute for Transfusion Medicine, the Clinic of Nuclear Medicine at the University Medical Centre Ljubljana, and the Institute of Biochemistry and Molecular Genetics at the Faculty of Medicine, University of Ljubljana. It is a non-randomized, single-center, open-label, phase I exploratory study. The study will include 10 patients (intervention group) and 10 healthy volunteers (control group) (Figure 1).

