**Primary**		
Evaluation of the safety of administration of allogeneic MSCs	Adverse event assessment (CTCAE v.5 criteria): pain at application site, mouth sensation, infection	From the start of therapy to the last follow-up (days 1, 5, 28, and 120)

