### Data Monitoring Committee

As a body independent of studies, sponsors and competing interests, the Ethics Committee of the Institute of Oncology Ljubljana is responsible for reviewing and monitoring all ongoing studies conducted at the clinic. Each year during the study, the principal investigator prepares an annual report on the progress of the study, registered adverse effects and SAEs, which is evaluated by the aforementioned committee.

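### The termination rule gives two stopping triggers that disagree on relatedness and grade, and ties the 24-hour notice to a severity grade labelled serious

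*Protocol article*

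**What the plan says.** Termination guidelines states two rules in consecutive sentences.

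- First: "The study will be terminated early if serious adverse events are noted during the intervention or follow-up". There is no condition on cause, grade or number of events.
- Second: it names allergic reaction, injection site infection and any "other local or systemic event assessed as possibly/probably/surely related to the intervention", and adds that such an event "graded according to CTCAE v5.0 grade 3 or higher (serious adverse reaction, SAR) will be considered a discontinuation criterion".

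Once a SAR is registered, the principal investigator informs the study coordinator within 24 hours. The national pharmacovigilance centre and the institute's Ethics Committee are informed afterwards, with no time limit given.

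Three other places bear on this:

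- Data Monitoring Committee makes the same Ethics Committee the monitoring body. It receives an annual report covering "registered adverse effects and SAEs, which is evaluated by the aforementioned committee". The article uses the term SAE here in its own right and defines it nowhere.
- Eligibility criteria lists infection at the graft site as a reason to remove a patient after enrolment, with no condition on grade or cause. A patient removed before the effect has been evaluated is replaced, so that the number stays at 10.
- Table 1 gives the primary safety outcome as "Adverse event assessment (CTCAE v.5 criteria): pain at application site, mouth sensation, infection".

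**The concern.** Safety is the primary objective, and this is the only stopping rule the article states. By the authors' account it is also the first evaluation of this cell source for xerostomia. The rule should give the same answer whoever applies it, but its two sentences differ on whether cause matters and on whether grade matters. They also differ in their terms: adverse event in one, adverse reaction in the other.

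The second sentence also uses a severity grade as the definition of serious. Severity describes how intense an event is. Seriousness, as usually understood, describes its consequence for the patient. Because the 24-hour notice depends on the grade-based label, urgent reporting follows intensity alone.

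At stake are whether the trial ends on an event that the treatment did not cause, and whether a related serious event of lower grade is reported promptly.

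**Working it through.** **Step 1: apply each sentence to the same event.** I take the relatedness and grade conditions in the second sentence to apply to every event it lists.

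| Event | First sentence | Second sentence | 24-hour notice |
|---|---|---|---|
| Serious, judged unrelated | Stops study | Not met | No |
| Related, serious, below grade 3 | Stops study | Not met | No |
| Related, grade 3 or higher, severe but not serious in the usual sense | Met only if grade 3 is taken to mean serious | Met | Yes |
| Related, grade 3 or higher, and serious | Stops study | Met | Yes |

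The sentences clearly agree only in the last row. The first two rows give opposite decisions. The third depends on a definition that the article does not give.

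**Step 2: compare with the patient-level rule.** A graft-site infection removes the patient under Eligibility criteria, and the patient is replaced if the effect has not yet been evaluated. If the infection is related and grade 3 or higher, Termination guidelines makes it a discontinuation criterion. Both rules then apply to one event. One leads to a replacement patient and the other to the end of enrolment, and neither section refers to the other.

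**Step 3: size.** The plan has no figure to reproduce: it gives no event rate and reports no sample size calculation. The number treated is 10 (Methods and design). Every risk below is an assumption.

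For a per-patient risk p of an unrelated SAE over the 4-month follow-up, the chance of at least one in 10 independent patients is 1 − (1 − p)^10:

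- p = 0.03: 1 − 0.97^10 = 1 − 0.737 = 0.263
- p = 0.05: 1 − 0.95^10 = 1 − 0.599 = 0.401
- p = 0.10: 1 − 0.90^10 = 1 − 0.349 = 0.651

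These are stopping probabilities under the first sentence. Under the second, the same events stop the study with probability 0.

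Now add a related risk r, with related grade 3 or higher events also counted as serious. The related-only reading gives 1 − (1 − r)^10. The any-SAE reading gives 1 − [(1 − r)(1 − p)]^10. With r = 0.02 and p = 0.05:

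- related only: 1 − 0.98^10 = 0.183
- any SAE: 1 − (0.98 × 0.95)^10 = 1 − 0.931^10 = 0.511

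Over r from 1% to 10% and p from 2% to 10%, the gap runs from 0.06 (r = 10%, p = 2%) to 0.59 (r = 1%, p = 10%). It is zero only when p = 0.

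**The case against.** The best defence is that the first sentence states a principle and the second makes it operational, so that related events of grade 3 or higher are the only trigger. That is a natural way to read a general statement followed by a specific one, and it may be what was meant. The text does not say so, however. The terms change between the sentences, and the annual report keeps SAEs as a category of its own. If that reading is right, the first sentence is wrong as written and still needs correction.

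A second defence is that a journal article leaves SAE definitions to the full protocol. This holds for the missing definition alone. It does not cover two rules that the article itself states and that disagree.

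A third is that the assumed rates have no support in the article. The Discussion reports no SAEs in an earlier ten-patient, four-month study of allogeneic cells at the same number per gland. That is fair, and it is why the probabilities are only an illustration. Ten event-free patients do not exclude such rates: at a true risk of 5% or 10%, that result has probability 0.95^10 = 0.60 or 0.90^10 = 0.35.

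A reader might also infer four stronger points that the article does not support:

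- *A related serious event below grade 3 escapes the stopping rule.* It still meets the first sentence. Only the second criterion and the 24-hour notice miss it.
- *The monitoring body learns of events only once a year.* Each SAR goes to the Ethics Committee, which is that body. What is missing is a time limit for that notice.
- *Discontinuation might mean the patient only.* The heading and the preceding sentence point to the study, and patient removal is listed elsewhere. Saying so outright would still help.
- *Pain from injections given without anesthesia makes stopping likely.* No rate for such pain is given. Counting related grade 3 pain is a clinical threshold, not a contradiction.

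**Conclusion.** The concern holds as a conflict within the stated stopping rule. The two triggers give opposite decisions for an unrelated SAE and for a related serious event below grade 3, and the latter gets no 24-hour notice. A related grade 3 or higher injection site infection falls under both a patient-replacement rule and a study-stopping rule. These conclusions come from the text and need no assumed rates.

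The size in probability terms does depend on assumptions: independent patients, 10 treated, and unrelated SAE risks of 3% to 10%. On those, the first sentence stops the study with probability 26% to 65% and the second with probability 0. These figures show how far the readings can diverge and are not a forecast. Nothing here says which trigger is clinically right.

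**What to change.** 1. Reconcile the two sentences of Termination guidelines into one trigger. State whether relatedness is required and that the trigger applies to the study.
2. Define seriousness separately from CTCAE grade, and tie the 24-hour notice to seriousness. If a grade-based criterion is kept, give it a name that does not use the word serious.
3. Reconcile this section with the subsequent-exclusion and replacement text in Eligibility criteria, so that a graft-site infection leads to one stated course.
4. Give a time limit for the onward notice to the Ethics Committee, which already receives SARs.

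The investigators and the committee choose the clinical threshold. The cost is protocol wording and a short amendment, with no added procedures.

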### Confidentiality

On all documents collected for data analysis, patients will be identified by code only. The log of subject identification data will be maintained by the principal investigator. The name or other information that might reveal the identity of the patient will not be included in any document that leaves the research center and will not be used for clinical research data analysis. As a research participant, the patient has the right at any time to obtain information about the personal data collected and processed by the research provider, to request their correction or deletion, and to complain to the supervisory authorities, i.e. the Information Commissioner of the Republic of Slovenia and the Data Protection Commissioner of the Institute of Oncology Ljubljana.

### Data Monitoring Committee

As a body independent of studies, sponsors and competing interests, the Ethics Committee of the Institute of Oncology Ljubljana is responsible for reviewing and monitoring all ongoing studies conducted at the clinic. Each year during the study, the principal investigator prepares an annual report on the progress of the study, registered adverse effects and SAEs, which is evaluated by the aforementioned committee.

### Availability of data and materials

Electronic study records will be stored on the hospital server and will be accessible via password-protected network computers. Data will be retained for up to 10 years, after which they will be deleted.

### Statistical methods

Since this is an exploratory study, no formal sample size calculation was performed.

Data will be managed in databases with Excel spreadsheets and analyzed with statistical analysis software such as SPSS, GraphPad Prism, or similar tools. Changes in absolute values and percent deviations from baseline salivary flow rate values before and after the procedure will be analyzed and compared at different time points within the intervention group; baseline values will also be compared with those of the control group. Numeric variables will be compared with paired t tests or nonparametric tests if the assumptions for parametric tests are not met.

The scores of the individual items of the VAS questionnaire and the Xerostomia questionnaire will be summed, and the total score is linearly transformed into a scale from 0 to 100.^29,30^ Scoring and interpretation of the EORTC QLQ-H&N35 questionnaire will be performed according to EORTC guidelines.^31^

Comparisons of MRI, ultrasound, scintigraphy, and analysis of core-needle biopsies taken before and after procedure will be descriptive in nature.

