**Secondary**		
Efficacy of the procedure	Measurement of unstimulated/stimulated salivary flow and saliva composition	During recruitment, day 28 and 120 post-procedure
	Assessment of subjective degree of xerostomia (questionnaires)	During recruitment, days 28 and 120 after the procedure
		Immediately after the procedure (day 0)
	Scintigraphic evaluation of grafting, retention, and migration of allogeneic MSCs	During recruitment, on days 28 and 120 after the procedure
	Assessment of patients’ quality of life	
Radiological changes of the salivary tissue	Magnetic resonance imaging (MRI): volume, signal, and diffusivity changes	During recruitment, on days 28 and 120 after procedure
	Ultrasonography (US): consistency (firmness)	
Functional changes of the salivary tissue	Scintigraphy with ([99mTc]TcO_4_^−^ (pertechnetate): uptake of radioisotope in parenchyma, ejection fraction	During recruitment, on days 28 and 120 after procedure
Morphological changes of the salivary tissue	Core needle biopsy specimens: composition, inflammatory infiltrate, metaplasia, reactive changes	During recruitment, on day 120 after the procedure

CTCAE v.5 = Common Terminology Criteria for Adverse Events version 5.0; MSCs = allogeneic mesenchymal stromal stem cells

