### Eligibility criteria

Patients who were successfully treated with (chemo)radiotherapy for squamous cell carcinoma of the oropharynx >2 years ago and have grade 2 or 3 xerostomia after radiotherapy according to the Common Terminology Criteria for Adverse Events (CTCAE) v.5.0 scale will participate in the study.^24^ Inclusion and exclusion criteria will be used to determine whether they can be included in the study (Table 2).

**TABLE 2. j_raon-2023-0052_tab_002:** Inclusion and exclusion criteria

**Inclusion criteria**	**Exclusion criteria**
Squamous cell carcinoma of the oropharynx, UICC TNM (8^th^ ed.) stage cT1–2N+ or cT3–4cN0–3 M0, treated with curative intent RT (TD 66–70 Gy, bilateral neck irradiation) with or without concurrent chemotherapy	Newly diagnosed malignant tumor anywhere in the body within the last two years
Two years or more after treatment with no evidence of locoregional recurrence or systemic metastasis	Active smoker
Nonsmoker or former smoker (quit smoking ≥ 2 years ago)	Use of xerogenic medications (e.g., tricyclic antidepressants, antipsychotics, decongestants, bronchodilators, antihypertensive agents such as beta blockers and diuretics, antihistamines, hypnotic sedatives, opioids, and muscle relaxants)
Mean radiation dose > 26 Gy to each of the parotid glands and > 35 Gy to each of the submandibular glands	Other salivary gland disorders (e.g., Sjoegren's syndrome, scleroderma, sialolithiasis, etc.)
Grade 2 or 3 xerostomia as assessed by the CTCAE v5.0 scale	Patients receiving anticoagulant therapy that cannot be discontinued during the procedure
Clinically decreased salivation and hyposalivation (unstimulated total salivary flow of 0.05–0.20 ml/min)	Pregnancy or planned pregnancy within the next two years
Age between 18–75 years	Breastfeeding
Both sexes	Active, uncontrolled infection
Signed “Informed Consent Form” to participate in the study	Other medical (including psychiatric) conditions that, in the opinion of the investigators, preclude safe administration of the planned therapy and completion of follow-up visits
	Known substance abuse or alcoholism

CTCAE v.5 = Common Terminology Criteria for Adverse Events version 5.0; RT = radiotherapy: TD = tumor doses; UICC = *Union for International Cancer Control*

Criteria for subsequent exclusion of patients from the study are: pregnancy, infection at the graft site, allergy to local anesthetics or citric acid, and withdrawal of consent to participate in the study.

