### Pre- and post-treatment assessment

After being informed about participation in the study and signing the Informed Consent form, patients will undergo the following tests and complete the following questionnaires during the 4-week period before MSC application, i.e., the procedure (Table 3). The same measurements will be performed and questionnaires completed at both the 4-week and 4-month follow-up, with the exception of core needle biopsy and salivary gland scintigraphy (these will be repeated only at the 4-month follow-up). All procedures in the study are listed in Table 3.

**TABLE 3. j_raon-2023-0052_tab_003:** Procedures of the study

**Procedures**	**Inclusion**	**Intervention**	**Follow-up examinations**			

	**W4→0**	**D0**	**D1**	**D5**	**D28**	**D120**
Patient screening with clinical and objective evaluation of xerostomia^1^	X					
Complete blood count, biochemistry	X				X	X
Coagulation profile	X					
Measurement of unstimulated and stimulated salivary flow rate	X				X	X
Determination of salivary composition	X				X	X
Magnetic resonance imaging	X				X	X
US elastography	X				X	X
Scintigraphy with [99mTc]Tc-HMPAO labeled MSCs		X				
Scintigraphy with (*[99mTc]TcO_4_^−^*)	X					X
Core needle biopsy of the gland^2^	X					X
Visual Analog Scale questionnaire	X				X	X
Xerostomia Questionnaire	X				X	X
EORTC QLQ-H&N35	X				X	X
Toxicity assessment, CTCAE v.5		X	X	X	X	X

CTCAE v.5 = Common Terminology Criteria for Adverse Events version 5.0; D = day; EORTC QLQ-H&N35 = European Organisation for Research and Treatment of Cancer Quality of Life Questionnaire Head and Neck Module; MSCs = allogeneic mesenchymal stromal stem cells; US = ultrasound; W = week; [99mTc]*HMPAO = T*echnetium 99m-hexamethylpropyleneamine oxime; *[99mTc]TcO_4_^−^* = *T*echnetium 99m-pertechnetate

1 Inclusion criteria, see Table 2.

2 From the parotid gland: the first 5 patients included in the study; from the submandibular gland: the last 5 patients included. The gland on the side that received a higher dose of radiation will be punctured.

The study also involves 10 volunteers (control group) who do not participate in the procedure. They will sign the Informed Consent to Participate in the Study and provide saliva samples for the measurement of unstimulated and stimulated salivary flow and for the determination of salivary composition (for comparison with the intervention group).

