In addition, Lynggaard *et al*. published encouraging results on the treatment of radiation-induced xerostomia with allogeneic adipose-derived MSCs.^39^ The use of allogeneic MSCs offers numerous logistical advantages: surgical intervention is no longer required to obtain the starting material, and the quality of the final preparations can be better controlled.^40^ In this study, 25×10^6^ MSCs were inserted into each submandibular gland and 50×10^6^ MSCs were inserted into each parotid gland in ten patients; the follow-up period was four months. During this period, an increase in mean unstimulated salivary flow was measured from an initial 0.13 ml/min to 0.18 ml/min. Stimulated salivary flow also increased after therapy from 0.66 ml/min to 0.75 ml/min. Patients’ subjective perception of an improvement in xerostomia was confirmed by questionnaire results, and no serious adverse events were reported during the study period.^39^

Recently, a dose-escalating phase I study protocol (3 + 3 design) was published for the treatment of radiation-induced xerostomia in patients with head and neck cancer with interferon-gamma-stimulated autologous bone marrow stromal cells.^41^ The results of this study are not yet available. However, in a pilot study, the same group has already used MSC prepared in this manner in six patients who received a single injection of 10×10^6^ MSC into a single mandibular salivary gland and found that the therapy was well tolerated and showed a trend toward improvement in salivary volume and quality of life.^42^

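### Unstimulated flow decides entry and appears also to be the baseline, so regression to the mean can produce a change without any effect; an arithmetic mean of percent changes would add an upward bias

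*Protocol article*

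**What the plan says.** - **Entry (Table 2).** Patients must have "unstimulated total salivary flow of 0.05–0.20 ml/min".
- **Timing (Table 1).** Flow and composition are assessed as follows: "During recruitment, day 28 and 120 post-procedure".
- **Schedule (Pre- and post-treatment assessment, Table 3).** After consent, "patients will undergo the following tests and complete the following questionnaires during the 4-week period before MSC application, i.e., the procedure". One pre-procedure column, W4→0, holds both the screening evaluation of xerostomia (footnoted to the inclusion criteria) and the flow measurement.
- **Collection (Measurement of unstimulated total salivary flow rate).** There is one collection before the procedure, one at 4 weeks and one at 4 months. No replicate or post-eligibility baseline is described.
- **Analysis (Statistical methods).** "Changes in absolute values and percent deviations from baseline salivary flow rate values before and after the procedure will be analyzed and compared" within the intervention group, by paired t tests or nonparametric tests. No alpha is given.
- **Comparator (Course of the study).** The healthy volunteers are examined once and not followed. They enter the analysis only as a comparison at baseline.
- **Size.** "The study will include 10 patients (intervention group) and 10 healthy volunteers (control group"), and "Since this is an exploratory study, no formal sample size calculation was performed".

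**The concern.** Selecting patients on a noisy measurement and then measuring change from that same reading invites regression to the mean. People admitted because one reading was unusually low tend to read higher next time, and people admitted because it was unusually high tend to read lower. With a single treated arm and controls measured once, the data cannot separate this drift from an effect of the cells.

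Percent change raises a second, independent issue. Dividing by a small, noisy baseline makes the arithmetic mean of individual ratios exceed 1 when nothing has changed.

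The study hypothesis is that the treatment is both safe and effective, and the Discussion says that the results will inform later trials and be compared with other groups' results. An apparent gain could therefore be carried forward as a treatment effect. If only one baseline is collected, later analysis cannot create an independent one.

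**Working it through.** The plan states no effect size, power or variability, so there is no figure to reproduce. The check asks what the planned comparison shows when the cells do nothing.

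**Inputs from the article:** entry window 0.05–0.20 ml/min; n = 10 treated; paired t test.

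**Assumptions not in the article:** log-normal flow; candidate-pool median m of 0.05 to 0.20 ml/min; between-person log SD σ of 0.5 or 0.7; within-person CV of 20%, 30% or 40%; two-sided alpha 0.05, so a false significant increase has nominal probability 2.5%.

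**Model:** t ~ N(log m, σ²); qualifying reading x₀ = exp(t + e₀); follow-up x₁ = exp(t + e₁); e₀ and e₁ independent N(0, s²) with s² = ln(1 + CV²). A patient is kept if 0.05 ≤ x₀ ≤ 0.20. There is no treatment effect.

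**Step 1. Qualifying reading used as baseline** (simulation, 3 million draws per scenario; each range covers both σ and all three CVs):

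| Pool median (ml/min) | Mean absolute change (ml/min) | Geometric mean ratio | False significant increases, n = 10, absolute scale |
|---|---|---|---|
| 0.05 | −0.007 to −0.001 | below 1 | about 1% or less |
| 0.08 | 0 to +0.006 | 0.95–0.99 | about 1–2% |
| 0.10 | +0.002 to +0.012 | 1.00 | about 3% |
| 0.13–0.20 | +0.005 to +0.040 | 1.01–1.19 | about 4–17% |

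The sign turns on where the pool lies relative to the window, which has a floor as well as a ceiling. Its centre on the log scale is √(0.05 × 0.20) = 0.10. Below that, the geometric mean ratio falls under 1; above it, the ratio exceeds 1.

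A wider grid, with medians up to 0.30 and within-person log SD up to 0.5, reaches +0.090 ml/min and about 41% false significant increases at its extreme.

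**Step 2. Scale against the only benchmark in the article.** In the earlier allogeneic study, "an increase in mean unstimulated salivary flow was measured from an initial 0.13 ml/min to 0.18 ml/min". That is 0.18 − 0.13 = +0.05 ml/min, or 0.05/0.13 = 38% as a ratio of means. For pool medians of 0.13–0.20 and CV 30%, the null change is +0.011 to +0.025 ml/min. That is 0.011/0.05 = 22% to 0.025/0.05 = 50% of the earlier change. As a ratio of means it is about +9% to +18%, the figure to set beside 38%. The mean of individual percent changes in the same scenarios is larger, +12% to +21%, but it is on a different scale.

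**Step 3. Independent baseline x_b, not used for eligibility.** The mean absolute change is 0 and the geometric mean ratio is 1.00 in every scenario. False significant increases on the absolute scale are about 2%. The mean of individual ratios stays above 1:

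E[x₁/x_b] = exp(s²) = 1 + CV²

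- CV 20%: 1 + 0.04, or +4%
- CV 30%: 1 + 0.09, or +9%
- CV 40%: 1 + 0.16, or +16%

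The two biases need different remedies. A second baseline removes the selection effect but not the ratio effect. The log ratio removes the ratio effect but, measured from the qualifying reading, still carries the selection effect (last row of the table).

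**The case against.** Several points against the concern are fair.

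- **The baseline is inferred.** Table 3 lists screening and flow measurement as separate rows within a four-week window. A separate baseline may exist, in which case one sentence would settle the selection point.
- **Averaging percent changes is not stated.** Absolute change is also planned and nonparametric tests are allowed. The CV² bias applies only to an arithmetic mean of individual percentages. With an independent baseline, a median percent change or a ratio of means does not carry it.
- **The pool may be low.** Candidates must have grade 2 or 3 xerostomia and mean doses above the stated thresholds to all four glands, so a pool centred at or below 0.10 ml/min cannot be excluded. The earlier study's baseline mean of 0.13 ml/min, with entry criteria described as comparable, hints at a higher pool, but only if this trial's baseline turns out similar.
- **Within-person variation is assumed.** The collection protocol fixes time of day, room, physician, hydration and fasting, which should reduce it.
- **Efficacy is secondary.** Safety is the primary objective, and no lead efficacy measure is named.

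These points limit the size and certainty of the concern. They do not remove it: a flow window at entry, one described pre-procedure reading, change measured from baseline and no followed comparator are all in the text.

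A reader might infer that a clear improvement will appear even if the cells do nothing. The documents do not support that. The bias can be positive, near zero or negative, and at n = 10 it reaches significance in a minority of trials even in the less favourable settings of the table.

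**Conclusion.** The concern holds in a limited form. As described, the change in unstimulated flow may include regression to the mean, and nothing in the design would reveal it. Under the stated assumptions the null change runs from about −0.007 to +0.040 ml/min across pool medians of 0.05–0.20. False significant increases are about 4–17% for medians of 0.13–0.20 and about 3% or less for medians of 0.10 or below, against a nominal 2.5%. This rests on the inference that the qualifying reading is the baseline, and on a pool and a within-person variability that the documents do not give.

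The percent-change bias of +4% to +16% is separate and conditional on an arithmetic mean being reported.

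It would go too far to call this an inflated main efficacy result, or to extend it to all flow data. Stimulated flow is not an entry variable and is affected only indirectly, and a comparison of day 28 with day 120 does not use the qualifying reading. The point merits a change to the plan but does not touch the primary safety objective.

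**What to change.** 1. **Separate baseline.** After eligibility is confirmed and before injection, repeat the unstimulated collection under the conditions already set out for it, and use that reading as the baseline. Do not use it to re-screen, or the selection returns. The cost is one more non-invasive 10-minute collection per patient with its preparation (fluid intake the day before, fasting, the morning slot, the same room and physician), placed at an already planned visit where possible. If a separate baseline is already intended, say so.
2. **Scale.** Replace percent deviation with the log ratio to baseline, reported as a geometric mean ratio with 95% confidence interval and a stated floor for zero flows, alongside absolute change. This costs nothing beyond choosing the floor.
3. **If no second baseline is taken.** State that the within-group change in unstimulated flow may include regression to the mean and cannot by itself support a conclusion on efficacy. This costs one sentence.
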